**12.8.3 Management of creatinine clearance results**

Study medication will be adjusted according to modified Tenofovir dose adjustment for renal impairment guidelines (Gilead Sciences).10

|  | Creatinine Clearance | | |
| --- | --- | --- | --- |
|  | ≥50 mL/min | 30–49 mL/min | < 29 mL/min |
| Recommended Dosing Interval | Every 24 hours | Every 48 hours | Stop study medication |

**13. Statistical summary**

The aim of this study is to determine if daily oral tenofovir 300 mg prevents HIV infection and is safe among IDUs in Thailand.

**13.1 Safety outcome**

Based on the AIDSVAX B/E vaccine trial, conducted 1999-2003 among IDUs enrolled from the same 17 BMA drug treatment clinics, we would expect a baseline SAE rate of about 7% during the year participants take study drug (Unpublished data). Assuming a sample size of 1000 per arm, table 3 shows the power to detect incremental increases in reported SAEs among tenofovir recipients compared to the placebo recipients using a 2-tail test and a 0.05 level of significance.

Table 3. Power to detect differences in reported SAEs among placebo and tenofovir recipients.

| Placebo Recipients | Tenofovir Recipients | Power |
| --- | --- | --- |
| 7% | 8% | 11% |
| 7% | 9% | 34% |
| 7% | 10% | 64% |
| 7% | 11% | 86% |
| 7% | 12% | 96% |
| 7% | 13% | 99% |

In summary, we have 80% power to detect an SAE rate above 11% among tenofovir recipients (4% greater than the 7% expected among placebo recipients).

**13.2 Effectiveness outcome**

Efficacy analysis is designed to determine if tenofovir efficacy to prevent HIV infection exceeds a threshold level of 10%. A lower threshold of 10% was selected in order to provide a result that can guide public health actions. HIV incidence during the AIDSVAX B/E HIV vaccine trial was 3.4 per 100 person-years. We suspect HIV incidence among IDUs in Bangkok has declined due to HIV prevention activities of BMA drug treatment clinic staff and changes in drug use (i.e., less heroin, more midazolam and methamphetamines)5. In order to ensure that there is sufficient power to achieve the study’s primary objective, to determine if tenofovir prevents HIV infection, we will use an endpoint-driven study design. Based on simulations assuming tenofovir efficacy of 50%, 67%, and 90% and a 1-tail alpha of 0.025, we determined power to provide a result with a lower limit 95% CI > 10% (Table 4).

Table 4. Power to demonstrate tenofovir efficacy with 95% CI >10%

| Estimated Tenofovir Efficacy | Expected Endpoints by Group | | | Power to show tenofovir efficacy with lower limit 95% CI > 10% |
| --- | --- | --- | --- | --- |
| Tenofovir | Placebo | Total |
| 50% | 12 | 24 | 36 | 37% |
| 67% | 9 | 27 | 78% |
| 90% | 3 | 33 | 99% |
| 50% | 13 | 27 | 40 | 49% |
| 67% | 10 | 30 | 82% |
| 90% | 4 | 36 | 99% |
| 50% | 14 | 30 | 44 | 54% |
| 67% | 11 | 33 | 86% |
| 90% | 4 | 40 | >99% |

If tenofovir efficacy is 67%, we have 82% power to demonstrate at least 10% tenofovir efficacy with 40 endpoints. A human post-exposure prophylaxis study suggests tenofovir efficacy to prevent HIV infection will exceed 67%.8

**13.3 Measures to minimize bias**

Multiple methods will be used to reduce bias:

- Randomization of participants to treatment arms
- Blinding of treatment arms (participants, study staff, data analysts)
- Using ACASI to ask risk behavior and adherence questions
- Immediate tracking for missed visits

**13.4 Randomization**

Study participants will be randomly assigned (1:1) to receive tenofovir or placebo using permuted blocks. The study arm assignment list will be generated by an independent statistician and the assignment codes will be known only to the statistician, Gilead, and the DSMB.

**13.5 Blinding**

Gilead Sciences, Inc. will supply matching placebo and tenofovir tablets. Tablet bottles will also be labeled with the participant ID so study clinic staff can dispense medication corresponding to the assigned treatment arm while remaining blinded. Using this method the participants, study clinicians, data management staff, monitors, statisticians, and investigators actively involved in the trial will not know which participants are taking tenofovir and which are taking placebo.

**13.6 Unblinding procedure**

The randomization code will be held by a statistician at CDC, Atlanta and a person to be identified at Gilead Sciences, Inc. Unblinded information will be provided to the principal investigator if needed in an emergency to guide treatment decisions for any participant. At the conclusion of the study, when primary analyses are complete and the study is unblinded to the investigators, participants will be offered the opportunity to learn into which arm they were randomized.

**13.7 Analysis plan summary**

All randomized patients will be included in the analysis. The analysis will be performed on an intention-to-treat basis. Data from participants lost to follow-up will be censored at the last contact. To assess the success of randomization, a summary of baseline variables by study arm will be tabulated. Continuous data will be summarized with descriptive statistics, including n, mean, standard deviation, minimum, maximum, median and interquartile range. Categorical data will be summarized using counts and percents. A significance level alpha=0.05 will be used to perform significance testing and construct confidence intervals. Heterogeneously distributed variables will be regarded as potential confounders and will be adjusted for in multivariable modeling. Missing data will be summarized by treatment groups, and missing patterns will be assessed using graphical and modeling approaches and an appropriate multiple imputation technique will be applied.24 All analyses will be done using SAS version V8 (Cary, NC, U.S).

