**6. Study objectives**

**6.1 Primary objectives**

- To determine if daily oral tenofovir 300 mg prevents HIV infection among IDUs
- To determine if daily oral tenofovir 300 mg is safe when given to HIV-uninfected IDUs

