**7.1 Primary endpoints**

The primary efficacy endpoint will be measured by:

- Rates of HIV seroconversion measured at monthly intervals

The primary safety endpoints will be measured by:

- The frequency of Grade 3 or 4 renal or hepatic function laboratory toxicities or clinical toxicities in blinded tenofovir and placebo arms, as defined by the Gilead-modified NIAID Adult Common Toxicity Tables, and which cannot be directly attributed to a cause other than study medications
- The frequency of adverse clinical events in tenofovir and placebo arms

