**8.2 Inclusion criteria**

- 20-60 years of age
- Report injection drug use in the 12 months before screening
- Possess documentation of Thai National Identification number
- Laboratory values as follows within 2 weeks before enrollment:
  - HIV oral fluid test non-reactive at screening and pre-enrollment visits
  - Hemoglobin  9 gm/dL
  - ALT and AST  2.5 x upper limit of normal (ULN)
  - Total bilirubin  1.5 mg/dL
  - Serum amylase  1.5 x ULN
  - Serum phosphorus 2.2 mg/dL
  - No evidence of current or chronic Hepatitis B infection by serology
  - Calculated creatinine clearance 60 mL/min by the Cockcroft-Gault formula where creatinine clearance in mL/min =

Male: (140 – age in years) x (wt in kg)

72 x (serum creatinine in mg/dL)

Female: (140 – age in years) x (wt in kg) x 0.85

72 x (serum creatinine in mg/dL)

- Willing to abstain from sexual intercourse or use effective contraception during the trial (oral, injection, or barrier) (women)
- Pass the comprehension test
- Willing and able to provide informed consent for study participation
- Available and committed to DOT or monthly follow-upfor at least 12 months

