**10.3.7 HIV and additional testing in scheduled and exit visits**

If OraQuick test of oral fluid is non-reactive, the participant will be informed that there is no evidence of HIV infection. In order to ensure that daily oral tenofovir does not lead to OraQuick non-reactive test results among HIV-infected volunteers, HIV confirmatory nucleic acid testing (NAT) will be done on sera available from volunteers who test OraQuick non-reactive.

If OraQuick HIV testing is reactive, study medication will be stopped, and the participant will be informed that the test is reactive and that blood tests are required to confirm the result. If the participant agrees**,** blood will be drawn and confirmatory testing done (i.e., EIA and, if necessary Western Blot) and the participant will complete the risk assessment and adherence questionnaire.

At the follow-up visit in 2 weeks, participants will receive post-test counseling and results of confirmatory testing. Participants, who test positive on confirmatory HIV testing, will have HIV-1 viral load, HIV-1 genetic characterization, antiretroviral drug resistance and CD4 testing and will be referred for follow-up care. Participant specimens from previous visits will be tested to determine if the participant was in the HIV window period when they previously tested HIV negative by oral fluid testing.

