**13.9 Efficacy analysis**

The study hypothesis is that HIV incidence will be lower among participants receiving tenofovir than among participants receiving placebo. A log-rank statistic will be used to test the efficacy of treatment.25 The efficacy of treatment will be estimated as

Efficacy = 1 – *RR*

where *RR* is the hazard ratio estimated from a discrete time proportional hazards regression model with an indicator variable representing treatment arm. Confidence intervals for efficacy can be calculated using the confidence limits for the *RR*.

All analyses will be performed on an intention-to-treat basis. Rates of HIV seroconversion with Poisson 95% exact confidence intervals will be used to summarize the data. Discrete time proportional hazards regression will be applied to adjust the treatment effect for age and gender and for other demographic or behavioral variables, which, despite the randomization, were heterogeneously distributed between the study arms.

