**Appendix C. Bangkok Tenofovir Study Laboratory Specimen Testing**

| **Test** | **Specimen** | **Visits** | **Assay** | **Assay site** |
| --- | --- | --- | --- | --- |
| HIV infection | Oral transudate (swab) | Screening, enrollment, and monthly visits | OraQuick (Orasure) | On-site clinic lab |
| HIV confirmatory testing | SST tube (9.5 ml) | OraQuick reactive only | WB, EIA (Biorad) | BMA Lab |
| Chemistries* | Screening visit, M1, M2 and every 3 months | Automated analyzer | BMA Lab |
| HBV serology** | Screening visit | EIA (Dade, Berhing) |
| CBC | EDTA tube (5 ml) | Screening visit, M1, M2 and every 3 months | Automate Analyzer | BMA Lab |
| CD4 | EDTA tube (5 ml) | All seroconverters | Flow cytometry (BD) | TUC lab |
| HIV plasma viral load | Amplicor Monitor (Roche) |
| HIV-1 subtyping | Peptide serotyping (CDC) |
| Pregnancy test | Urine (women) | Screening, enrollment and monthly visits | Rapid β-HCG (Commercial Science) | On-site clinic labs |
| HIV antiretroviral resistance testing | EDTA tube (5mL) | All seroconverters | TruGene HIV-1 genotyping  (Visible Genetics) | TUC Lab |
| TDF levels | serum | All seroconverters in TDF arm and random 10% of non-seroconverters | HPLC | To be determined |
| HIV sequencing | PBMC | All seroconverters | Sequencing | TUC Lab |

*Chemistries: BUN, creatinine, electrolytes, ALT, AST, bilirubin, amylase, phosphorus, calcium, alkaline phosphatase

**hepatitis B virus surface antigen (HbsAg), anti-HBs IgG, anti-HB core IgG

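### Infections already present at randomisation count as efficacy endpoints, and the plan does not fix how infection is defined or dated

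*Protocol*

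**What the plan says.** - **Population.** Section 13.7: "All randomized patients will be included in the analysis". Sections 13.7 and 13.9 both specify intention to treat.
- **Endpoint.** Section 7.1 names "Rates of HIV seroconversion measured at monthly intervals". Section 13.9 adds: "Rates of HIV seroconversion with Poisson 95% exact confidence intervals will be used to summarize the data".
- **Entry test.** Section 8.2 requires "HIV oral fluid test non-reactive at screening and pre-enrollment visits". No nucleic acid test is required for entry.
- **Back-testing.** For confirmed positives, Section 10.3.7 says: "Participant specimens from previous visits will be tested to determine if the participant was in the HIV window period". The same section plans NAT on available sera from OraQuick non-reactive volunteers, to check that tenofovir does not mask infection. Neither result is given a consequence for the analysis.
- **Terms.** The objective in Section 6.1 is "To determine if daily oral tenofovir 300 mg prevents HIV infection among IDUs", and Section 8 closes enrolment at 24 HIV infections. Section 13.10 triggers the efficacy analyses at 24 and 40 seroconversions.

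**The concern.** An oral-fluid antibody test is non-reactive for some time after infection, so some participants will be infected before their first dose. Prophylaxis cannot prevent those infections. Randomisation spreads them about evenly over the arms, so counting them adds events with a hazard ratio near 1 and dilutes the estimate. Because the trial is event-driven, each one also takes the place of an informative event in the 24 and the 40. The protocol expects such cases, since it collects the data that would identify them, but sets no rule for using the result.

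Separately, infection and seroconversion differ for exactly the participants for whom NAT is planned: those NAT-positive but OraQuick non-reactive. If tenofovir delays antibody response, this would happen in one arm only, so the endpoint status and date of such cases should be settled before unblinding.

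**Working it through.** **Inputs from the protocol.** 40 endpoints, 67% efficacy, lower limit above 10%, one-sided alpha 0.025 and stated power 82% (Section 13.2 and Table 4); 1:1 allocation (13.4); 2,400 participants or 24 infections over 36 months (Section 8); past incidence 3.4 per 100 person-years, suspected to have fallen (13.2).

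**Assumed.** An undetected window of 14-28 days and current incidence of 1.0-3.4 per 100 person-years. The documents give neither.

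**1. Reproduce the 82%.** Given 40 events, the tenofovir count X is binomial with probability HR/(1+HR).
- At the 10% threshold, p0 = 0.9/1.9 = 0.474. P(X ≤ 12) = 0.019 and P(X ≤ 13) = 0.041, so success means X ≤ 12.
- At 67% efficacy, p = 0.33/1.33 = 0.248 and P(X ≤ 12) = 82.8%. At two-thirds efficacy it is 82.1%. The stated figure reproduces.

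**2. Let k of the 40 be present at randomisation.** Now X = Bin(40 − k, 0.248) + Bin(k, 0.5). Expected tenofovir events are t = (40 − k) × 0.248 + k/2, and expected efficacy is 1 − t/(40 − t).

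| k | Tenofovir v placebo events | Expected efficacy | Power |
|---|---|---|---|
| 0 | 9.9 v 30.1 | 67.0% | 82.8% |
| 1 | 10.2 v 29.8 | 65.9% | 80.4% |
| 2 | 10.4 v 29.6 | 64.7% | 77.8% |
| 3 | 10.7 v 29.3 | 63.6% | 75.0% |
| 4 | 10.9 v 29.1 | 62.4% | 72.0% |
| 6 | 11.4 v 28.6 | 60.0% | 65.6% |

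If these infections are excluded and 40 incident ones are accrued, the k = 0 row applies.

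**3. How many to expect.** Number = participants × incidence × window/365.
- Low: 2,400 × 0.010 × 14/365 = 0.9.
- High: 2,400 × 0.034 × 28/365 = 6.3.

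The high figure is probably too high, because at 3.4 per 100 person-years enrolment would stop at the 24th infection. With even enrolment of 800 a year, no losses and 67% efficacy, pooled incidence is 0.034 × 1.33/2 = 0.0226. Then 24 infections need 24/0.0226 ≈ 1,060 person-years. Person-years accrue as 400t², so t ≈ 1.63 years and about 1,300 are enrolled. That gives 1,300 × 0.034 × 28/365 = 3.4. A range of 1-4 is therefore reasonable, with 6 as an outer value.

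**4. Scale of the NAT question, for illustration.** Start from the 10 v 30 split in Table 4 and add 1, 2 or 3 uncounted tenofovir infections. Efficacy goes from 66.7% to 63.3%, 60.0% or 56.7%. The lower 95% limit (log ratio, variance 1/tenofovir + 1/placebo) goes from 31.8% to 26.8%, 21.9% or 16.9%. The documents give no basis for choosing among these counts.

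**The case against.** All-randomised intention to treat is a standard primary population, and dating rules are often left to a SAP, which is not shown. Other text leans toward incident infection: Section 13.9 frames the hypothesis as HIV incidence, and Section 10.3 lists precise timing of infection among the reasons for frequent visits. If back-testing dated an infection before enrolment, that person would contribute no time at risk. The bias is also conservative and cannot by itself create a false claim of efficacy.

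Much of this stands, and it limits the size of the point. It does not remove it. The protocol nowhere adopts the dating that would exclude these cases, and a SAP that dropped them would contradict Section 13.7.

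A reader might infer that NAT-positive, antibody-negative infections are not counted. No section says so. Section 10.3.7 orders NAT to find them, and the objective speaks of infection. Oral testing recurs at every monthly visit and at exit (Table 2), so most would turn reactive later and be counted late rather than lost. What remains is an undefined endpoint status and date, which matters most for cases still antibody-negative at the last test.

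**Conclusion.** The point holds for infections present at randomisation. Followed literally, the plan counts them as endpoints and toward both event targets. With 1-4 among the 40, an expected 67% efficacy becomes 66-62% and power drops from 83% to 80-72%; two are enough to bring power below 80%. The table follows from the protocol's own design figures. The number of such infections does not: it rests on the assumed window and incidence, and could be as low as about one.

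On NAT-positive, OraQuick non-reactive cases, the conclusion is only that the terms are inconsistent and the rule is missing. It is also tempting to say the efficacy estimate is biased in a known direction overall. The documents do not support that: the two effects run in opposite directions, neither count is given, and the net sign cannot be determined.

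**What to change.** - **Endpoint (Sections 7.1 and 13.9).** Define it as HIV infection confirmed by EIA/WB or NAT, dated at the earliest positive specimen. Use the same term in Sections 8 and 13.10.
- **Population (Sections 13.7 and 13.9).** Make the primary analysis modified intention to treat, excluding participants shown to be infected on a pre-randomisation specimen. Decide this blind to arm, by the same rule in both arms.
- **Event targets.** Do not count those infections toward 24 or 40.
- **Sensitivity.** Keep the all-randomised analysis.
- **State the limit.** Table 2 lists no enrolment blood draw, and Appendix C schedules chemistries and CBC at "Screening visit, M1, M2 and every 3 months". The specimen to use is therefore the screening serum already drawn. Entry criteria require "Laboratory values as follows within 2 weeks before enrollment", so infections acquired between screening and the first dose may stay in the analysis. The protocol should say so.

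**Cost.** Mostly wording. Some additional NAT on stored screening sera may be needed, since back-testing is now promised only for confirmed positives and NAT only on available sera. A few randomised participants leave the primary population, on a criterion fixed before randomisation and judged without knowledge of arm.

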**10.3.5 Follow-up visits for newly HIV infected participants**

All newly HIV infected participants will be followed at 4 weeks, 8 weeks, and every 16 weeks (4 months) after confirmation of HIV infection until the study ends. Participants will receive counseling, have a pregnancy test (women), and blood will be collected for laboratory testing. Participants will complete a risk behavior questionnaire using an ACASI at the 16 week (4 month) visits.

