**12.2 Adverse event (AE)**

An AE is any unfavorable and unintended sign (e.g., an abnormal laboratory finding), symptom, or disease temporally associated with the use of an investigational product, whether or not considered related to the product.

An AE **does not** include:

- Diseases or conditions present or detected prior to taking study drug (i.e., pre-existing) which do not worsen during the trial
- Medical or surgical procedures (e.g., endoscopy, appendectomy); but the condition that leads to the procedure is an AE (e.g., bloody diarrhea, appendicitis)
- Situations where an untoward medical event has not occurred (e.g., hospitalization for elective procedure or for social reasons/convenience)
- Overdose of either study drug or concomitant medication without any signs, symptoms, or hospitalization

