**12.8.1 Management of laboratory abnormality *(except serum creatinine elevation)* or clinical event**

**Grade 1 or 2:** Continue study medication at the discretion of the study physician.

**Grade 3 or 4:** May continue study medication, at the discretion of the study physician, for up to 3 days while values are confirmed.

**Confirmed grade 3:** If unrelated to study drug by above definitions, may continue dosing. If causal relationship to study drug possible by above definitions, withhold drug until toxicity returns to < grade 3 then retest to confirm participant is HIV negative then restart study drug. If toxicity > grade 3 recurs, permanently discontinue dosing and follow at scheduled study visits until toxicity resolves.

**Confirmed grade 4:** If unrelated to study drug by above definitions, may continue dosing. If causal relationship to study drug possible by above definitions, permanently discontinue study drug and follow at scheduled study visits until toxicity resolves. Do not rechallenge.

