**13.8 Analysis of safety outcomes**

AEs, SAEs, and abnormal laboratory test results will be compared between the study arms. Factors that may be associated with AEs will be analyzed. AEs will be organized by frequency, severity, and relationship to study agent in each study arm. Rates of AEs among tenofovir and placebo recipients will be compared using chi-squared tests. Longitudinal analysis of AEs will be examined using generalized estimating equation (GEE) logistic regression. The time to adverse event will be examined using Kaplan-Meier plots, log-rank tests, and Cox proportional hazards models to compare the incidence of AEs.

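### All-randomized intention-to-treat is the only analysis basis stated for safety; an on-drug safety analysis should be added beside it

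*Protocol*

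**What the plan says.** Section 13.7 sets the analysis basis for the whole trial: "All randomized patients will be included in the analysis. The analysis will be performed on an intention-to-treat basis". The only censoring rule there is "Data from participants lost to follow-up will be censored at the last contact"; nothing is tied to stopping study drug. Section 13.9 repeats intention-to-treat separately for efficacy, so 13.7 is not naturally read as an efficacy-only rule.

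Section 13.8 covers safety: "Rates of AEs among tenofovir and placebo recipients will be compared using chi-squared tests". It adds GEE logistic regression, Kaplan-Meier plots, log-rank tests and Cox models. It names no on-drug set and no at-risk window.

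Two other sections bear on this. Section 9.5 gives the reason for monitoring adherence: both safety and efficacy are best assessed in the light of actual medication use. Section 14.2 lists adherence-adjusted analyses for the interim reports, but for efficacy outcomes alone.

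Time off drug is foreseen. Section 9.6 covers participants who run out of drug after a missed visit or whose drug is interrupted for a transient event. Section 10.3.6 covers those released from a correctional facility after a missed appointment and those who have lost access to medication or cannot take it.

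**The concern.** Safety is one of two primary objectives (6.1), and the reassuring result is no difference between arms. For efficacy, an intention-to-treat comparison that includes time off drug is conservative, because poor adherence makes a good drug look weaker. For safety the same dilution runs the other way: poor adherence makes a toxic drug look safer.

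The protocol recognises the principle in 9.5 and acts on it only for efficacy in 14.2. The 7% SAE rate in Section 13.1 is also framed as the rate during the year on study drug. The power basis is therefore an on-drug rate, while the stated analysis basis is not on-drug. At stake is how confidently a null safety result can be read if a material share of follow-up is spent off drug.

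**Working it through.** **Inputs.** From Section 13.1 and Table 3: 1,000 participants per arm, SAE rate 7% on placebo and 11% on tenofovir, "using a 2-tail test and a 0.05 level of significance", stated power 86%. The off-drug share *f* is not in the protocol. It is assumed, shown from 10% to 40%, and taken as equal in both arms.

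**Step 1: reproduce Table 3.** Two-proportion normal test with continuity correction:

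power = Φ{ [ |p1 − p0| − 1/n − 1.96·SE0 ] / SE1 }

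Here SE0 = √[2·p̄(1−p̄)/n] and SE1 = √[(p0(1−p0) + p1(1−p1))/n].

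For p0 = 0.07, p1 = 0.11 and n = 1,000: p̄ = 0.09, SE0 = 0.01280, SE1 = 0.01277. Then (0.04 − 0.001 − 1.96 × 0.01280)/0.01277 = 1.09, and power is 86.2%. For tenofovir rates of 8% to 13% the formula gives 11.6, 34.7, 64.3, 86.2, 96.3 and 99.3%, against 11, 34, 64, 86, 96 and 99% in Table 3. The table is reproduced.

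**Step 2: count all follow-up.** If off-drug time carries no excess risk, the tenofovir rate becomes 0.07 + 0.04(1 − f), and placebo stays at 0.07.

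**Step 3: count on-drug time only.** Events in both arms scale with time at risk: 0.07(1 − f) v 0.11(1 − f).

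| f | All follow-up: rates | Power | On-drug: rates | Power | Net cost (points) |
|---|---|---|---|---|---|
| 0% | 7.0 v 11.0% | 86% | 7.0 v 11.0% | 86% | 0 |
| 10% | 7.0 v 10.6% | 79% | 6.3 v 9.9% | 82% | 3 |
| 20% | 7.0 v 10.2% | 70% | 5.6 v 8.8% | 77% | 7 |
| 30% | 7.0 v 9.8% | 59% | 4.9 v 7.7% | 70% | 11 |
| 40% | 7.0 v 9.4% | 47% | 4.2 v 6.6% | 62% | 16 |

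Net costs are taken before rounding (for example 78.9% v 81.9% at 10%).

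**Step 4: read the table.** The absolute excess is the same in both counts, 0.04(1 − f). The on-drug count removes the background events of the off-drug time, which lowers the variance and keeps the rate ratio at 0.11/0.07 = 1.57. Counting all follow-up, the ratio falls to 9.8/7.0 = 1.40 at f = 30%. The fair measure of what the stated basis costs is the last column. The drop from 86% also contains exposure that no analysis can recover.

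**The case against.** The strongest reply is that an all-randomized safety comparison is not an error, and that a safety set and an on-treatment window are commonly left to the SAP, which is not at hand. That stands for the missing window taken alone. It does not answer the rest: 13.7 states a rule, does not confine it to efficacy, and would be carried into a SAP that follows it. Nor does it explain why 14.2 adjusts efficacy but not safety for adherence, given 9.5.

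Several stronger readings are tempting, and the documents do not support them.

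- A reader might infer that safety is explicitly counted over all follow-up. No sentence says so; it is inferred from intention-to-treat with censoring at last contact. The adverse-event definition also requires a "symptom, or disease temporally associated with the use of an investigational product, whether or not considered related to the product", which links events in time to product use.
- A reader might infer that HIV infections themselves enter the adverse-event comparison, so that fewer infections on tenofovir would mask harm. No section says they are counted. The first primary safety endpoint (7.1) drops events directly attributable to another cause. Section 12.7.3 gives diagnosed infectious diseases as examples of events judged unrelated, and 13.8 plans that "AEs will be organized by frequency, severity, and relationship to study agent in each study arm". Only the second primary safety endpoint, all adverse clinical events, leaves the question open. Section 12.7.1 was not in the text available, so a rule there cannot be ruled out.
- A reader might count follow-up after HIV infection as a large block of off-drug time: "All newly HIV infected participants will be followed at 4 weeks, 8 weeks, and every 16 weeks". Those visits list no adverse-event assessment, 10.3.4 treats the confirmation visit as an exit visit, and about 40 of 2,400 participants (1.7%) are concerned.
- Follow-up after stopping for toxicity is a weak source of dilution. Section 12.8.1 says "permanently discontinue study drug and follow at scheduled study visits until toxicity resolves", so it does not run to study end. These participants have already had the event, and keeping them preserves evidence of harm.

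**Conclusion.** The point holds in a limited form. The protocol's only stated basis for safety is all-randomized intention-to-treat, with no on-drug analysis beside it and adherence adjustment planned for efficacy alone. Where off-drug time carries no excess risk, this biases the safety comparison towards no difference.

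Under an assumed off-drug share of 10% to 40%, equal in both arms, the net loss of power for 7% v 11% SAEs is about 3 to 16 points. The full falls to 79%, 70%, 59% or 47% should not be charged to intention-to-treat. If harm carries over after stopping, the dilution is smaller. The loss would also be smaller for the first primary safety endpoint to the extent that its attribution limit already removes background events.

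No figure in Table 3 is wrong. Whether HIV infection counts as an adverse event under the second primary safety endpoint needs only a one-line clarification; the documents do not show that it distorts the comparison.

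**What to change.** Keep the all-randomized safety comparison. In Section 13.8 add a supplementary on-drug analysis of the primary safety endpoints and SAEs, with time at risk running from first dose to a fixed, prespecified number of days after last dose, built from dispensing, pill-count and diary data. In Section 14.2 extend the adherence-adjusted interim analyses to safety outcomes. As a minor clarification, say whether HIV infection is counted as an adverse clinical event.

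The cost is one extra set of safety tables from data already collected (9.5, Table 2). The drawback is real: the on-drug comparison is not fully protected by randomisation. Because drug is stopped for toxicity, its cut-off is informative and can miss delayed harm. It must therefore be shown beside the all-randomized result and not replace it.
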